### 4.5. Quality Control

To reduce the potential bias and ensure the quality of this trial, all acupuncturists and assessors will be required to receive standard training prior to the beginning of the trial. The content of the training course is provided by the protocol, including recruitment, interventions, and assessment process. Whether the data is complete and accurate will be monitor by a qualified clinical trial expert from the Clinical Research Center of the First Affiliated Hospital of the Henan University of Chinese Medicine. All clinical trial experts are independent of the sponsor. In addition, a quality control team will be established to supervise whether the experimental procedure meets the standard guideline. Statistical analysis will be performed when the total number of samples collected reaches 89 cases. The primary investigator will obtain these interim results and will decide whether to continue the trial. We will stop the trial if the efficacy of the patients in the experimental group is much lower than the other two groups in the outcomes of the interim data [26].

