### 2.3. Blinding

This is a single-blinded study; because of the nature of acupuncture treatment, none of the acupuncturists involved in this trial can be blinded to the assignments. Patients will be told that they will receive one of the three effective interventions randomized after enrolment. Each patient will know the type of treatment that they accepted, but they will not know the other two types. The intervention of each patient will be performed in a personal space separated to refrain the communication between patients and will be asked to wear an eye patch when they receive treatment. Data managers and statisticians are not clear on the allocation of patient groups. Therapists, data managers, and statisticians are not allowed to communicate with others about the treatment of patients.

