### 4.2. Safety Evaluation and Adverse Events

Any adverse events and how they are dealt with will be recorded throughout the treatment process. Adverse events related to acupuncture treatment included severe pain, fainting, bleeding, or other any discomfort. During the intervention period, the researchers will pay close attention to the patient's condition. If any discomfort occurs to the patient, the intervention will be stopped immediately and the patient's condition will be dealt with accordingly. Any medical occurrence detailed information will be reported in detail in case report forms (CRFs). The primary researchers will review all adverse events periodically, and the Ethics Committee will have access to the interim results.

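### Interim results at 89 of 177 cases go to the primary investigator, who decides on continuation under a criterion with no outcome or margin

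*Protocol article*

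**What the plan says.** Section 4.5 (Quality Control) sets the timing: "Statistical analysis will be performed when the total number of samples collected reaches 89 cases". It then names the recipient and the decision-maker: "The primary investigator will obtain these interim results and will decide whether to continue the trial". The criterion follows: "We will stop the trial if the efficacy of the patients in the experimental group is much lower than the other two groups". That criterion compares the experimental group with the other two, so the results that the investigator receives must be by arm.

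Section 4.2 gives one other body sight of the data: "the Ethics Committee will have access to the interim results". It gives that committee no part in the decision. The independent experts in section 4.5 check whether data are complete and accurate, not whether the trial goes on.

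On blinding, section 2.3 says that "none of the acupuncturists involved in this trial can be blinded to the assignments" and, of patients, "Each patient will know the type of treatment that they accepted, but they will not know the other two types". It also says: "Data managers and statisticians are not clear on the allocation of patient groups". Blinding of the outcome assessors is not stated. The ban on discussing treatment covers therapists, data managers and statisticians; the primary investigator is not listed.

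**The concern.** Two things are fixed badly.

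**Who sees and decides.** Halfway through, the person leading a single-centre trial learns which arm is ahead and then carries on running the trial. The acupuncturists know every allocation and patients know their own treatment. MAS, one of the two primary outcomes in section 2.9, is graded by hand, and section 5.2 itself describes the spasticity measures in current use as highly subjective. Knowledge of the trend can reach the rest of the trial through the choice of patients approached, the routine drug and rehabilitation treatment given alongside, and the grading.

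**What the rule is.** The efficacy it refers to could be RMS or MAS (the primary outcomes) or the effectiveness rate used for the sample size in section 2.7. No margin is attached to *much lower*. The chance of stopping a treatment that is no worse, and the chance of continuing one that is worse, are then settled by whoever reads the rule, after the data are seen.

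**Working it through.** **Inputs from the protocol article.** Look at 89 cases (4.5); 177 patients, 1:1:1, 59 per group (2.7); effectiveness rates 90% for GV-EA, 75% for conventional EA and 60% for rehabilitation; alpha 0.05, type 2 error 0.1, minimum 53 per group, dropout 10% (2.7).

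**Assumptions.** The split of 89 across arms is not given; I use 30/30/29 (GV-EA with 30) and, for comparison, 30/30/30. The interim outcome is not named; I use the effectiveness rate because it is the only outcome for which the article gives figures. It is illustrative: it is not among the listed primary or secondary outcomes. The margins are mine, chosen only to show the range.

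**Step 1: the plan's own figure.** Three-group chi-square test on 2 df with rates 0.90, 0.75, 0.60. The mean is 0.75, so w² = [(0.15² + 0 + 0.15²)/3] / (0.75 × 0.25) = 0.015/0.1875 = 0.08. Power from the noncentral chi-square with noncentrality 3n × 0.08 is 0.896 at n = 52 and 0.902 at n = 53, so 53 per group is reproduced. Then 53/0.9 = 58.9, rounded up to 59, and 3 × 59 = 177. The sample size does not bear on this point beyond supplying the rates.

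**Step 2: position of the look.** 89/177 = 50.3%, and 177 − 89 = 88 patients remain if the trigger is the 89th enrolment. If it means 89 patients with 4-week data, some of the 88 will already be in treatment or finished, so 88 is an upper limit.

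**Step 3: chance of stopping for margin m.** With X₀, X₁, X₂ the responders in GV-EA and the two controls,

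P(stop) = Σₖ P(X₀ = k) × P(X₁/n₁ − k/n₀ ≥ m) × P(X₂/n₂ − k/n₀ ≥ m),

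using exact binomial probabilities. Each cell gives 30/30/29, then 30/30/30.

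| Reading of the rule: GV-EA below both controls by at least | No difference (75/75/75) | True 15-point deficit (60/75/75) |
|---|---|---|
| 10 points | 8.8%, 11.0% | 53%, 58% |
| 15 points | 3.4%, 3.2% | 36%, 35% |
| 20 points | 1.1%, 1.5% | 21%, 25% |

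Under the planned rates (90/75/60) the chance is below 0.1% for every margin.

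**Step 4: reading the table.** Moving the margin from 10 to 20 points cuts the wrong-stop risk from about 9–11% to about 1%, and cuts the chance of catching a true 15-point deficit from about 55% to 21–25%. The criterion as worded does not choose between these.

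**The case against.** **The type I error.** A reader might infer that an unadjusted look at half the data inflates the false-positive rate of the final 0.05 test. The article does not support that. The only stop it describes is for a worse experimental arm, and such a stop cannot produce a false claim in favour of GV-EA. Inflation would need an efficacy test at the look, and none is described.

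**Any shortfall as a trigger.** A reader might count every look at which GV-EA is numerically below both controls, which happens in 28–29% of looks when there is no difference. The wording asks for more than that, so this figure does not describe the rule. If the planned rates are right, a wrong stop is practically excluded.

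**The route to bias.** The trial is called single-blinded, not open-label. Patients are kept apart, wear eye patches and do not know the other two treatments. Data managers and statisticians do not know allocation. The RMS co-primary is recorded by instrument. Nothing says that the primary investigator treats or assesses patients, so an effect on grading is inferred. This limits the concern mainly to MAS, the rated secondary scales, recruitment and co-treatment. It does not remove it: assessor blinding is not stated, and the ban on discussing treatment does not list the investigator.

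**Detail held elsewhere.** The outcome and margin may be set in the full protocol, the analysis plan or the reference cited for the rule. That could settle the number. It would not settle the recipient and the decision-maker, which section 4.5 fixes; a document that moved them elsewhere would contradict it.

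**Conclusion.** The point holds as a design weakness that should be corrected before the look. Section 4.5 gives results by arm, and the decision, to the trial's leader in a single-centre trial with unblinded acupuncturists and a rater-graded co-primary outcome. Up to about 88 patients would be recruited, treated or graded after the trend is known. *Alone* would be right for the decision but not for access, since the Ethics Committee may also see the results.

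The size of the bias cannot be calculated from the article. What can be calculated is how loose the criterion is: about 9–11%, 3% or 1% wrong stops, and about 55%, 35% or 21–25% stops for a true 15-point deficit, at margins of 10, 15 and 20 points. These figures rest on about 30 patients per arm, a true control response of 75%, and the effectiveness rate standing in for an outcome that the rule does not name. The final 0.05 test is not invalidated.

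**What to change.** - **Section 4.5, recipient and decision.** Send interim results by arm only to the Ethics Committee, which already has access under 4.2, and have it make the continuation recommendation. The primary investigator receives only *continue* or *stop*.
- **Section 2.3, to match.** Statisticians are described there as unaware of allocation. They could, for example, prepare the interim table with arms coded A, B and C, with the code held by the Ethics Committee. Assign these codes independently of the Group A, B and C labels already in Table 1.
- **Section 4.5, rule.** Before the look, name which primary outcome *much lower* refers to and the margin, and state the chance of stopping under no difference and under a true deficit. The margin is the sponsor's choice. If it is already set in another document, a cross-reference is enough.
- **Section 4.5, purpose.** State that the look serves only to stop for a worse experimental arm and that no efficacy claim is made from it, so the final 0.05 test is unaffected. Say whether the 89 cases are enrolled or completed.

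The cost is wording in two sections; no patients or visits are added. The investigator gives up sight of the interim data, and the Ethics Committee takes on a decision role that it does not have now and must agree to.

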## 5. Discussion

Lower limb spasticity will severely limit the patient's trunk antigravity activity function and daily and social life ability recovery and even induce severe complications such as pneumonia and deep vein thrombosis [27]. It is of great significance to find effective treatment measures to reduce lower limb spasticity after stroke. This study is designed to evaluate the efficacy and safety of GV-EA in the treatment of poststroke lower limb spasticity.

### 5.1. Acupuncture Points Selection

The GV walks in the middle of the back and intersects with the three yang meridians of hand and foot and the Yang Link Vessel many times. Due to the connection between the GV and the yang meridians, it is also called “the sea of the yang meridians” [28]. Unblock Yang takes the regulation of Du as the first, so acupoints on the GV are selected. In this trial, the selected acupoints GV14, GV11, GV8, GV4, and GV3 are all the GV points. Among them, GV14 is the intersection of the GV and the three yang meridians of hand and foot, that is, “confluence of the yang”. GV8 acupoints mainly treat convulsions, strong spine, limbs, and tendons and have a good effect on spastic hemiplegia caused by stroke [29, 30]. EA at the above-mentioned acupoints can effectively promote the circulation of yang qi in the GV to the whole body. Blood flows with qi, and qi and blood flow to the end of the limbs so that the muscles and veins of the limbs can be nourished by qi and blood, thereby relieving limb spasticity.

### 5.2. Outcome Measurements Selection: Surface Electromyography (sEMG)

The sEMG evaluation is an objective method to obtain the electromyographic signal during muscle activity, which is achieved by placing surface electrodes on the muscle layer [31]. It can perform quantitative and qualitative analysis on the function of muscles and can study multiple muscles on the body at the same time. It has the advantages of noninvasiveness, safety and reliability, convenient operation, and objective quantification [32]. The evaluation of nerve and muscle function and rehabilitation effects of stroke patients has gained more and more attention. The muscle strength classification scale and muscle spasticity detection methods that are still in use until now are subject to great subjectivity; the detection results are difficult to accurately quantify and qualify so that subjective evaluation methods are questionable and limited in clinical applications [33]. And through the analysis of sEMG signal, it can reflect the level of motor unit recruitment and synchronization and can study the functional status and control mechanism of the nerve and muscle of stroke patients with hemiplegia to evaluate the rehabilitation effect and guide that rehabilitation process has become an important tool in the field of rehabilitation [34, 35].

One important limitation of our study is that as it is an acupuncture trial, it is impossible to execute double-blind procedures. To reduce this kind of bias, each group of patients will be treated in a different room, and each group of patients will be prohibited from talking. In addition, all the acupuncturists participating in this study will conduct unified training and strictly regulate the acupuncture operation to maximize the elimination bias. In addition to the required scales, sEMG is also used in the evaluation to reduce the interference of subjective factors. We expect that the results of this trial will provide evidence on the efficacy and safety of GV-EA in the treatment of poststroke lower limb spasticity. This will provide a practical and effective treatment method for the clinic, which has very important social significance.

## Figures and Tables

**Figure 1 fig1:**
[figure not shown]
Flowchart of the trial. GV-EA: Governor Vessel electroacupuncture; EA: electroacupuncture; RMS: root mean square; MAS: the Modified Ashworth Scale; FMA-LE: the Fugl–Meyer Assessment for Lower Extremity; MBI: the Modified Barthel Index.

**Table 1 tab1:** Qualification screening and informed consent will be completed before the assignment. After allocation, each patient will be treated within 4 weeks. The clinical outcome will be evaluated twice: after allocation and after treatment. Adverse events will be recorded on the case report form at any time during treatment.

Timepoint	Enrollment	Allocation	Treatment period			
	−1 week	0 weeks	1 week	2 weeks	3 weeks	4 weeks
*Enrollment*						
Eligibility screen	X					
Baseline	X					
Informed consent	X					
Medical history	X					
Merger disease	X					
Allocation		X				

*Interventions*						
Group A			X	X	X	X
Group B			X	X	X	X
Group C			X	X	X	X

*Assessments*						
RMS		X				X
MAS		X				X
FMA		X				X
MBI		X				X
Safety evaluation		X				X
Needle sensation			X	X	X	X
Adverse events			X	X	X	X

**Table 2 tab2:** Location of acupoints for treating poststroke lower limb spasticity.

Acupoints location	
Dazhui (GV14)	In the depression inferior to the spinous process of the seventh cervical vertebra (C7), on the posterior median line
Shendao (GV11)	In the depression inferior to the spinous process of the fifth thoracic vertebra (T5), on the posterior median line
Jinsuo (GV8)	In the depression inferior to the spinous process of the ninth thoracic vertebra (T9), on the posterior median line
Mingmen (GV4)	In the depression inferior to the spinous process of the second lumbar vertebra (L2), on the posterior median line
Yaoyangguan (GV3)	In the depression inferior to the spinous process of the fourth lumbar vertebra (L4), on the posterior median line

**Table 3 tab3:** The MAS specific scoring rules.

Modified Ashworth Scale	
1	No increase in muscle tone
1	Slight increase in muscle tone, manifested by a catch or by minimal resistance at the end of the range of motion (ROM) when the affected part(s) is (are) moved in flexion or extension
1+	Slight increase in muscle tone, manifested by a catch, followed by minimal resistance throughout the remainder (less than half) of the ROM
2	More marked increase in muscle tone through most of the ROM, but affected part(s) easily moved
3	Considerable increase in muscle tone, passive movement difficult
4	Affected part(s) rigid in flexion or extension

## Data Availability

No data were used to support this study.

## Abbreviations

GV-EA: Governor vessel electroacupuncture
EA: Electroacupuncture
sEMG: Surface electromyography
SPIRIT: Standard Protocol Items: Recommendations for Interventional Trials
CT: Computed tomography
MRI: Magnetic resonance imaging
PASS: Power analysis and sample size
SPSS: Statistical Package for the Social Sciences
RMS: Root mean square
MAS: Modified Ashworth Scale
FMA-LE: Fugl–Meyer Assessment for Lower Extremity
MBI: Modified Barthel Index
CRFs: Case report forms.
